### Secondary outcomes

Further outcomes are presented in Table 4 and cover changes over time in VAS pain scores, and changes over time assessed by three validated questionnaires: (1) the impact of lower back pain on daily life (the Rolland and Morris Disability Questionnaire (RMDQ) [27, 28]), (2) inappropriate fears and beliefs about lower back pain (the fear, avoidance, belief questionnaire (FABQ) [29]) and (3) a general measure of quality of life (the Euroqol Group 5 dimension, 5 level questionnaire (EQ-5D-5 L questionnaire) [30, 31]). Patients will also be questioned about how they perceive the acceptability of their symptoms, using the Patient Acceptable Symptom State (PASS) [33]. The overall opinion of the patient and the physician on the patient’s state of health (5-point Likert scale) will be recorded. Finally, per-patient health resource use will be quantified by estimating drug consumption, infiltrations, hospitalizations, imaging and sick leave. The latter will be used, in conjunction with the French national cost scale, to estimate the cost of care after 12 months of follow up for each patient (Table 4).

### Sample size

Data from two unpublished, open-label studies on typical patients receiving spa therapy indicate estimated rates of clinically relevant change in VAS pain scores of 47% (8/17) and 38% (10/26). Our hypothesis is that the proportion of patients experiencing improvement at 6 months will be 40% in the experimental arm (UCHE plus spa treatment) versus 25% in the control arm (UCHE only). Considering a type 1 risk level set at 4% (1% will be used for an interim analysis following the inclusion of the first 100 patients) and a type 2 risk level set at 20% (i.e. statistical power of 80%), the minimum sample size required is 322 participants. To maintain power for analysis on observed data and expecting a drop-out rate of approximately 10%, this estimate is increased to a total of 358 paricipants (179 per study arm).

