### Statistics

Statistical analyses will be performed by the Department of Medical Information at the University Hospitals of Montpellier, Montpellier, France, using the R programming environment [50] or SAS (enterprise guide V.7.1 or higher). An intention-to-treat structure will be implemented. The intention-to-treat population will include all randomised patients and will respect their allocations, regardless of whether or not they started the allocated interventions. Analyses may be adjusted according to clinical or inclusion criteria to take into account population heterogeneity. Though generally presented here, a more detailed statistical analysis plan will be drafted prior to the end of participant inclusion (and made available at https://osf.io/ahpwy/).

Descriptive statistics (for the total population and for each arm) will be provided as means with standard deviations for quantitative variables with normal distributions according to the Shapiro-Wilks test, or as medians with interquartile variables for other quantitative variables. Numbers and percentages will be provided for categorical variables.

As indicated in Table 4, the primary analysis is the comparison of the proportion of patients with a clinically relevant change in pain at 6 months; this will involve the uncorrected chi square (χ^2^) test for independent groups, or alternatively Fisher’s exact test if the conditions for the χ^2^ test are not met. We expect to perform an interim analysis of the number of patients in both groups with clinically relevant improvement as soon as there are 100 patients suitable for analysis with 6 months of follow up. The purpose of the latter is to assess futility, and a difference between arms (intervention – control) < 0 will stop the trial.

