As concerns secondary analyses, comparisons of qualitative variables will be performed in the same manner as for the primary analysis. The centrality of quantitative variables will be compared between arms using parametric (*t* test) or non-parametric (Mann Whitney test) analysis for independent groups, as appropriate. For longitudinal data, the preferred method will employ mixed models with patients set as a random effect and study arm as a fixed effect; an appropriate interaction term (group × time) will be used to detect differences between study arms in the rate of change. In addition, a medico-economic analysis comparing the two patient management strategies will be conducted according to international [51] and French recommendations [52]. A cost-utility analysis will be carried out, with utility values evaluated using the EQ-5D-5 L. The following direct medical costs will be considered: hospitalizations and consultations, transport, drugs and laboratory assessments.

Variables that are used for stratification (spa or presence of a professional activity) may be used in sub-group analyses. Covariate-interaction tests are the preferred method for detecting sub-group differences [53]. Statistical analyses will be adjusted on variables found to be imbalanced between arms. Sub-group tests will be considered as exploratory in nature.

The general hypothesis of the study supposes more improvement in the experimental arm as compared to the control arm. A difference will be considered statistically significant when the type I error rate is less than or equal to 0.05. As concerns missing data, patients lost to follow up will not be considered as withdrawn from the study but will be analysed as failures for the primary endpoint. Any deviations from the statistical analysis plan must be authorized by the study methodologist and will be thoroughly documented and justified in the study analysis report.

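### The final primary test is set at 4% in one section and 5% in another, and the 1% reserved for the interim pays for a futility-only look

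*Protocol article*

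**What the plan says.** Three statements in the protocol article bear on the threshold for the primary comparison.

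- **Sample size section.** The calculation uses a "type 1 risk level set at 4% (1% will be used for an interim analysis following the inclusion of the first 100 patients". This splits a 5% total into 1% at the interim and 4% at the end. The planning rates are "40% in the experimental arm (UCHE plus spa treatment) versus 25% in the control arm (UCHE only", power is 80%, and the result is 322 patients, raised to 358 for about 10% drop-out.
- **Statistics section, on the interim.** The look takes place "as soon as there are 100 patients suitable for analysis with 6 months of follow up". Its only rule is: "The purpose of the latter is to assess futility, and a difference between arms (intervention – control) < 0 will stop the trial". No efficacy boundary is given.
- **Statistics section, on significance.** "A difference will be considered statistically significant when the type I error rate is less than or equal to 0.05". The sentence does not set the primary analysis apart, and nowhere does the section say that the final primary test uses 0.04.

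**The concern.** Setting alpha aside for an interim makes sense only if the interim can declare efficacy. A look that can only stop the trial for lack of benefit gives no additional chance of a false positive, so it needs no share of alpha. The Sample size section implies an efficacy test. The Statistics section describes a look without one, and then applies the full 5%.

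The two sections therefore disagree on whether a final p-value between 0.04 and 0.05 is a positive result. The choice could be made after the result is known. The article states in its Discussion that there is no independent data and safety monitoring board, and it leaves continuation after the interim to the steering committee, so the written rule is the main safeguard.

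A smaller point is that the trigger is worded in two ways: after inclusion of 100 patients, or once 100 have six months of follow-up.

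**Working it through.** **Inputs.** From the Sample size section: control rate 0.25, experimental rate 0.40, power 80%, final alpha 4%, interim alpha 1%, 322 patients before drop-out and 358 after. From the Allocation and blinding section: 1:1 allocation. From the Statistics section: uncorrected chi-square test, threshold 0.05, interim on 100 patients. Sidedness is not stated; I assume two-sided, and one-sided 4% would give 260 patients, which does not match.

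**1. Which alpha produced the stated sample size?** With pooled variance and no continuity correction,

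n per arm = [z(1−α/2)·√(2·p̄·(1−p̄)) + z(0.80)·√(p₁(1−p₁) + p₂(1−p₂))]² / (p₂−p₁)²

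Here p̄ = 0.325, so 2·0.325·0.675 = 0.43875 (root 0.6624). The unpooled sum is 0.1875 + 0.24 = 0.4275 (root 0.6538). The squared difference is 0.15² = 0.0225, and z(0.80) = 0.8416.

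- α = 0.04: (2.0537·0.6624 + 0.8416·0.6538)² / 0.0225 = 162.2, that is 163 per arm, 326 in total.
- α = 0.05: (1.9600·0.6624 + 0.8416·0.6538)² / 0.0225 = 151.9, that is 152 per arm, 304 in total.

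At 4% the unpooled formula gives 320 and the arcsine formula 324, so the stated 322 lies inside the range for 4%. Then 322/0.9 = 357.8, which gives 358. At 5%, only a continuity-corrected calculation (330) comes near 322, and the planned test is uncorrected. The sample size rests on 4%.

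**2. Overall type I error under each reading.** Under the null hypothesis the interim and final statistics are approximately bivariate normal with correlation √(100/N), which is 0.557 for N = 322 and 0.529 for N = 358. The two-sided critical values are 2.576 (1%), 2.054 (4%) and 1.960 (5%). Overall alpha is one minus the probability that both statistics stay inside their limits.

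| Interim | Final test | Overall two-sided alpha |
|---|---|---|
| Efficacy test at 1% | 4% | 4.7% (simple sum 5%) |
| Efficacy test at 1% | 5% | 5.7% (simple sum 6%) |
| Futility only, stop ignored | 5% | 5% |
| Futility only, stop binding | 5% | 2.5% (normal); 2.6% (exact, 50 then 179 per arm) |

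The exact figure in the last row is slightly higher because an observed tie does not stop the trial.

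**3. Power cost of the 4% threshold.** Exact power of the uncorrected chi-square test at 40% against 25%, without the futility stop:

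| Patients per arm | Final 4% | Final 5% |
|---|---|---|
| 161 | 79.7% | 82.5% |
| 179 | 83.9% | 86.2% |

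The difference is 2.8 points at 161 per arm and 2.3 points at 179.

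**The case against.** The best defence reads the 0.05 as the overall error rate, made up of 1% and 4%. The sentence speaks of a type I error rate, stands in a general paragraph and covers secondary comparisons too. This reading is possible, but it does not fit well. The sentence is worded as the condition for calling a difference significant, no other sentence assigns 0.04 to the final primary test, and a 1% + 4% split needs an efficacy test that the interim as described does not have.

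Three further objections carry weight and limit the point.

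- The 5.7% arises only if an efficacy test at 1% is combined with a final test at 5%. Under the interim rule actually written, neither threshold exceeds 5%.
- The trial was sized for 4% and meets its 80% target there, so retaining 4% is conservative and leaves no shortfall.
- The trigger discrepancy is mostly wording. The primary outcome is measured at six months, so the look cannot take place at inclusion, and the Statistics section supplies the detail. A clarification is enough.

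It may also be said that the statistical analysis plan will settle the boundary. But this is not an omission left to that plan: both levels are fixed in this document, and they conflict.

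**Conclusion.** The point holds. The article fixes two thresholds for its only primary test, and it reserves 1% of alpha for a look that, as described, cannot use it. Whether a final p-value between 0.04 and 0.05 counts as positive depends on which section is followed.

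The consequence is bounded: overall alpha of about 5.7% in the worst combination, or about 3 points of power given up if the look is futility-only and 4% is kept. These figures assume two-sided testing, 100 patients at the interim, 322 to 358 at the end, and the planning rates of 40% and 25%. The modest numbers affect how serious the defect is, not whether it exists. The threshold for the main result has to be unambiguous before the interim data are seen.

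**What to change.** Choose one scheme and state it identically in the Sample size and Statistics sections.

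- **If the interim is futility-only**, as the Statistics section says: remove the 1% allocation, say that the look has no efficacy boundary, and test the final primary comparison at two-sided 0.05. The computed requirement falls to 304 (338 after 10% drop-out: 152/0.9 = 168.9, so 169 per arm), but N can stay at 358.
- **If stopping for efficacy at 1% is intended**: put that test in the Statistics section and give 0.04 there as the final threshold for the primary comparison. The planned N already matches this.

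The first follows the interim rule as written. The second keeps the alpha on which the trial was sized. Because recruitment has begun and the first scheme relaxes the sizing alpha, it should be documented before anyone sees interim results by arm.

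In either case, state the sidedness and use one trigger: the first 100 patients to reach the 6-month assessment. The cost is a sentence or two in each section and no additional patients.

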### Allocation and blinding

Following initial consent covering the UCHE intervention and subsequent baseline assessments, patients will be randomly assigned to either control or experimental groups in a 1:1 allocation ratio (Fig. 1, Table 3). In line with a single Zelen design [23, 24], patients randomised to the experimental group will be informed about the additional spa therapy intervention and invited to sign an additional consent form; furthermore, these patients can refuse spa therapy, but statistical analysis will be performed on an intention-to-treat basis. Patients allocated to the control group have already consented to the UCHE intervention and will proceed without information on spa therapy; this design is necessary to avoid bias associated with “resentful demoralisation” effects [24].

Allocation is performed using a computer-generated randomisation schedule and stratified by the recruiting investigator/spa (the latter are paired, but separate) and by whether or not the patient has a professional activity. Baseline evaluations and the subsequent randomisation are performed by the recruiting investigators through specific modules administered via a password-protected Internet-accessible electronic case report form (eCRF). The randomisation module will become accessible to investigators only after key elements of baseline data have been entered in the eCRF.

To blind the study as much as possible, follow-up assessments are performed during specific follow-up visits (see Table 3) by an “evaluating” physician, who is different from the “recruiting” investigator. Every attempt will be made to keep evaluating investigators blinded. Specifically, study participants will be instructed to not mention study participation or spa therapy to their evaluating physicians (at the end of the final follow-up visit, the study clinical research associate (CRA) will ask the evaluator a guess-the-group question in order to evaluate the success of blinding). As concerns follow-up care, emergency situations requiring specific unblinding procedures are not foreseen in this protocol. Finally, the statisticians will be blinded, i.e. study arms will be referred to as “A” or “B” when the database is presented for analysis. Unveiling of the study arms will occur after completion of planned statistical analyses.

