## Discussion

The LOMBATHERM’ protocol aims to document a thorough range of endpoints highly relevant to the targeted population of patients with low back pain, including changes in pain and symptom acceptability, associated disability, fears and beliefs and quality of life. Should the expected positive effects of spa therapy in addition to usual care be confirmed, a safe, novel physical therapy regimen will be added to the treatment arsenal available for these patients who are difficult to treat.

Care was taken to reduce sources of bias in as much as possible by selecting a clinically relevant primary endpoint and implementing a Zelen randomisation procedure (which eliminates “resentful demoralisation” effects [24]). Further advantages of the Zelen design are an improvement in patient blinding for the control arm, making treatment discussion with the patient more straightforward and closer to “routine” clinical practice, potentially increasing recruitment rates and decreasing post-randomisation withdrawal. However, a single-Zelen design also has a certain limitation that must be taken into account, i.e. the possibility of patient crossover between arms. The latter may dilute the treatment effect within an intention-to-treat analysis, thus providing an underestimated or conservative estimate [24].

Further limitations to the study include a lack of an independent data and safety monitoring board, which was deemed unnecessary due to the low-risk status of this trial. One must also consider the single-blind nature of the protocol, which is understandable given the impossibility of implementing full blinding of the patients receiving spa therapy. Furthermore, there is no way to guarantee the blinding of evaluators, which highly depends on patient collaboration. Nevertheless, the partial blinding of patients (control arm via the Zelen randomisation), the assessing physician, therapists and statisticians have all been addressed. The success of evaluator blinding will therefore be assessed by a guess-the-group question at the end of the final follow-up assessment.

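### The 10% drop-out inflation preserves 80% power for an observed-data analysis only; with lost patients counted as failures, N = 358 gives about 78% at the 4% level or about 80% at 0.05

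*Protocol article*

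**What the plan says.** The Sample size section assumes that the proportion improved at 6 months "will be 40% in the experimental arm (UCHE plus spa treatment) versus 25% in the control arm (UCHE only"). It sets these rates beside two small open-label series "on typical patients receiving spa therapy indicate estimated rates of clinically relevant change in VAS pain scores of 47% (8/17) and 38% (10/26"). The level is fixed with the words "Considering a type 1 risk level set at 4% (1% will be used for an interim analysis"), power is 80%, and the required number is 322. That number is then raised to 358 (179 per arm): "To maintain power for analysis on observed data and expecting a drop-out rate of approximately 10" per cent.

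The analysis is described differently. The Statistics section defines the intention-to-treat population as everyone randomised, as allocated, whether or not they started the intervention. On missing data it says that "patients lost to follow up will not be considered as withdrawn from the study but will be analysed as failures for the primary endpoint". The same section puts statistical significance at 0.05. It also plans an interim look at 100 patients with 6-month data, with a stop if the difference (intervention minus control) is below zero.

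Under the single Zelen design, patients learn of spa therapy only after they are randomised to it. Allocation and blinding says "these patients can refuse spa therapy, but statistical analysis will be performed on an intention-to-treat basis". On crossover between arms, the Discussion concedes: "The latter may dilute the treatment effect within an intention-to-treat analysis". The Sample size section states no allowance for refusal.

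**The concern.** The inflation and the missing-data rule belong to two different analyses. Dividing by 0.9 replaces the patients who drop out of a complete-case comparison and leaves the 15-point contrast intact. When lost patients stay in the denominator as failures, none need replacing, but both response rates shrink and so does the difference between them. The extra patients offset that shrinkage only in part.

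Refusal could act in the same direction. The quoted series are of patients who received spa therapy, whereas the randomised spa arm will include some who declined it.

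At stake is whether the published power figure describes the test that will be run. If it is too high, a null result would be read with slightly more confidence than the design supports.

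**Working it through.** **Inputs from the protocol article.** Rates 40% and 25%, level 4%, power 80%, drop-out 10%, N = 322 then 358 (Sample size); 1:1 allocation (Allocation and blinding); uncorrected chi-square test, lost patients as failures, 0.05 threshold, stop if the difference is below zero at 100 patients (Statistics). Two-sided testing is assumed; it is the reading that fits the stated N, since one-sided 4% would need only 260.

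**Formula.** With n per arm, pbar = (p1 + p2)/2, s0 = √[2·pbar(1 − pbar)] and s1 = √[p1(1 − p1) + p2(1 − p2)], power = Φ[(|p1 − p2|·√n − z·s0)/s1]. Here z = 2.054 at 4% and 1.960 at 5%.

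**Step 1: reproduce the plan.** For 40% versus 25% at 4%, the pooled formula needs 163 per arm (326), the unpooled version 320, and the arcsine version 161.5 per arm, about 322. The stated 322 is sound. Inflation: 322/0.9 = 357.8, rounded up to 358. With 161 observed per arm, power at 4% is 79.7%, so the stated 80% holds for an observed-data analysis.

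**Step 2: apply the missing-data rule.** With 10% lost in each arm and scored as failures:

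- p1 = 0.9 × 0.40 = 0.360 and p2 = 0.9 × 0.25 = 0.225, a difference of 13.5 points instead of 15.
- s0 = 0.6433 and s1 = 0.6362.
- At 4%: (0.135 × √179 − 2.054 × 0.6433)/0.6362 = 0.762, so power is 77.7% (exact enumeration of the chi-square test: 77.9%). Reaching 80% would need 380 in total.
- At 0.05: the argument is 0.857, so power is 80.4%, and 356 patients give 80%.

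The result depends on the loss rate. At 4%, equal loss of 5%, 15% or 20% per arm gives 80.9%, 74.2% or 70.5%.

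**Step 3: add the futility stop.** Assume 50 patients per arm at the interim and a binding stop. The chance of stopping at 36.0% versus 22.5% is about 5.4%. Simulated power becomes about 76% at 4% and about 79% (78.6%) at 0.05.

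**Step 4: illustrate refusal.** The protocol gives no rate. Assume that a fraction r refuse, that refusers respond at 25%, and that refusal is independent of loss. Then p1 = 0.9 × [0.40(1 − r) + 0.25r] and p2 = 0.225. Power with 179 per arm, before any futility stop:

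| Assumed refusal | p1 | Power at 4% | Power at 0.05 |
|---|---|---|---|
| 0% | 0.360 | 77.7% | 80.4% |
| 5% | 0.353 | 73.5% | 76.5% |
| 10% | 0.347 | 69.0% | 72.2% |
| 20% | 0.333 | 58.9% | 62.6% |

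**Step 5: relax the refusal assumptions.** If refusers are the first to be lost, p1 stays at 0.360 for refusal up to 10%, and power at 4% stays at 77.7%. At 20% refusal, p1 = 0.80 × 0.40 + 0.10 × 0.25 = 0.345 and power is 67.9%. If spa receivers respond at the pooled rate of the two series, 18/43 = 41.9%, an arm-wide 40% already absorbs refusal of 1 − 0.15/(0.419 − 0.25), about 11%. With 10% refusal and 10% loss, power is then 78.6% at 4% and 81.3% at 0.05.

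**The case against.** The strongest reply is that 40% and 25% are worded as rates in each arm. Since arms are defined by allocation, they might already count lost patients as failures. On that reading 179 per arm gives 83.9% power at 4%, and the inflation is a bonus that lets a complete-case analysis also keep about 80%. This is possible but fits the text poorly: an inflation for drop-out on observed data would not be needed for the primary analysis, and the protocol does not present it as support for a secondary one. What stands is that the wording of the 40% leaves open whether some refusal is already absorbed.

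A second reply is that the documented loss is small and vanishes at the 0.05 threshold, where power is 80.4% before the stop. That is correct. A reader might infer that 80% power is plainly not delivered; the document does not support so flat a statement, because the answer turns on which of its two significance levels governs the final test and on what the 40% represents.

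A reader might also take the 59% to 74% range in the refusal table as the trial's real power. The document does not support that either. Those figures need a refusal rate that it does not give, and independence of refusal and loss, and Step 5 shows how far they move when these assumptions change. The Discussion also openly says that crossover may make the estimate conservative, which tempers the risk of over-reading a null result.

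Finally, the futility cost assumes a binding stop. The Statistics section reads that way, but the section on the steering committee gives that committee the decision on continuation after the interim.

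**Conclusion.** The mismatch is real and its documented size is modest. Both 322 and 358 are computed correctly, but for an analysis that is not the primary one. Taking 40% and 25% as rates among observed patients, with 10% equal loss and two-sided testing, the planned primary test has about 78% power at 4% (about 76% with a binding stop) or about 80% at 0.05 (about 79% with the stop). Refusal can only be treated conditionally: it would lower power further unless the 40% already allows for it, by an amount the protocol does not let anyone fix. The point concerns the accuracy of the power statement; it does not put the primary test or its error rate in doubt.

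**What to change.** Keep N = 358 and revise the Sample size text:

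- Base the power statement on the lost-as-failure rates, 36.0% versus 22.5% at 10% loss.
- Reconcile the 4% in Sample size with the 0.05 in Statistics, and use the level that the final test will have. Restate power as about 78% at 4% or about 80% at 0.05, before the futility stop.
- Say whether 40% is the rate among all patients allocated to spa therapy, refusers included, or only among those who receive it.
- Add one sensitivity line for refusal (for example 5%, 10% and 20%, labelled as assumptions) and for the futility stop, saying whether that stop is binding.
- Keep the observed-data wording only if it is labelled as supporting a complete-case sensitivity analysis.

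The cost is a few sentences and, at 4%, a power figure about 2 points lower. No patients are added and the primary test is unchanged.
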